**Fig. 1 Fig1:**
[figure not shown]
Electrocardiogram (ECG) and cardiovascular magnetic resonance (CMR) examples in troponin positive COVID-19. Potential diagnoses include: no abnormalities detected, myocarditis, infarction, dual pathology and pericardial inflammation. First example shows a normal 12-lead electrocardiogram (ECG) and a normal CMR study. Second example shows myocarditis, with anterolateral ST segment flattening. CMR shows normal function but patchy mid-wall enhancement in the anterior and inferior wall (red arrows) with T2 map showing co-localised oedema. The third example shows myocardial infarction with ECG anterolateral ST changes and thinning of left ventricular (LV) wall predominantly in the anterolateral segment on the short-axis image (red asterisk); corresponding LGE image shows an ischaemic pattern transmural scar (red arrow); T1 maps show elevated T1 values in the lateral wall. The fourth example shows a case of dual pathology due to myocarditis and infarction. The ECG shows hyperacute T-waves in the anterolateral leads and the CMR study shows a short-axis cine with increased signal intensity in the anterior/anteroseptal segment (red asterisk). The two LGE images reveal an ischaemic scar in this area extending from subendocardium as well as an area of sub-epicardial enhancement in the inferior wall consistent with myocarditis (red arrows). The last case presents pericardial inflammation. The ECG shows widespread concave ST-segment elevation. The 4-chamber cine is unremarkable, whereas the corresponding LGE images show pericardial enhancement (red arrows)

Based on the possibility that myocardial injury may be relatively common in COVID-19 patients, and has been shown to be a marker of poor prognosis, further studies are required to clarify the pathophysiology of SARS-CoV-2 related myocardial injury. In particular, the nature of injury may suggest the need for therapeutic intervention, which may be specific (e.g. antithrombotic, anti-inflammatory), or non-specific e.g. heart failure treatment. Importantly, the nature and extent of myocardial injury may also help risk stratify patients both acutely and chronically, and for this, multi-time-point imaging is required to separate out cause and effect. Finally, the underlying risk factors for myocardial involvement and the impact on long-term clinical outcomes need to be investigated.

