### Recruitment process and data collection

Screening will be performed at an individual hospital level, with participating hospitals cross-referencing all admissions with a positive COVID-19 status (pathology/radiology diagnosis), with serum troponin results. This study will integrate two key aspects. Work package-1 will establish a national image repository for patients with COVID-19 who have CMR for clinical reasons. Work package-2 (objectives as outlined above) will use CMR to characterise the nature and extent of myocardial injury in a hospitalised but recovering patient population, who are serum biomarker (troponin) positive for myocardial damage.

The source data will include hospital records, National Health Service (NHS) health and social care records, clinical and office charts, laboratory and pharmacy records as well as digital images from radiology (chest X-ray/computed tomography/CMR) and cardiology (echocardiography/angiography/CMR). Patients in work package-1 who have a clinically indicated CMR and are troponin positive will be invited to join work package-2 for a follow-up CMR scan and assessment at 6 months. Clinical follow up for vital status and cardiovascular events at 12 months (and up to 5-years) will be performed by recruitment sites via local hospital electronic patient records, primary care records and by national data-linkage for other NHS databases.

Co-enrolment of patients in existing registries will be encouraged (e.g. ISARIC-4c and CAPACITY: Cardiac complicAtions in Patients with SARS Corona vIrus 2 regisTrY; NCT04325412). Also, as this is a longitudinal, observational study, co-enrollment with other UK COVID-19 studies/trials will be permitted.

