**Fig. 2 Fig2:**
[figure not shown]
Study flow diagram. COVID-19 patients, who have an elevated troponin, will be invited to participate in the study. Patients who are recruited undergo multimodality assessment at index visit: either during their hospital admission or within 28 days of discharge. Assessment includes a 12-lead ECG, CMR study, genetic and immunological blood tests, and Quality of Life questionnaires. Patients are subsequently invited for a second visit at 6 months. At this point they undergo a repeat CMR scan, quality of life assessments and 6-min walk test. Further follow up at 12 months will be conducted via examination of routine clinical data, available through general practitioners, electronic hospital records, NICOR and NHS Digital, and in collaboration with other nationally recognised COVID-19 studies

1)* CMR* Scans will ideally be performed pre-discharge or within 28 days of discharge, and then repeated at 6 months (± 4 weeks) from the date of admission and on the same scanner wherever possible. Scans will be performed on either a 1.5 T or a 3 T CMR system using multi-channel phased-array chest coils of any vendor, depending upon local availability. ECG gating will be employed for all cardiac gated sequences to ensure appropriate triggering. The main CMR protocol is in keeping with Society for Cardiovascular Magnetic Resonance (SCMR) recommended CMR protocols for scanning patients with active or convalescent phase COVID-19 [6], and it will take approximately 50 min to acquire, with an optional shortened and extended protocol dependent of patient preference and ability. An estimated glomerular filtration rate (eGFR) and haematocrit will be measured prior to each CMR scan. For patients with significant renal failure (eGFR < 30 ml/min/1.73 m^2^), late gadolinium enhancement (LGE) and post-contrast T1-mapping can be omitted and a contrast-free CMR scan performed.

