### Follow-up

Patients will be followed up at 6 months (± 4 weeks) from date of the diagnosis of COVID-19, and invited to have a second CMR scan, ECG, QoL assessment (SF-36v2 and EQ-5D-5L) and functional assessment (6MWT). In addition, routine clinical outcome data will be collated up to 5 years post-infection from: electronic patient records, general practice information systems, National Institute for Cardiovascular Outcomes Research (NICOR) and NHS Digital (eDRIS in Scotland).

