### Statistical analysis

Statistical analyses will be conducted after production of a signed statistical analysis plan and once baseline and follow-up data collection has been completed. Broadly, the statistical methods for each study objective will be as follows:to characterise the nature and extent of myocardial involvement in COVID-19 patients with an elevated troponin, analyses will be descriptive, and will involve estimation of prevalence with 95% confidence intervals (CIs);to assess how cardiac involvement and clinical outcomes associate with recognised risk factors for mortality in COVID-19 (age, sex, ethnicity and comorbidities) and with genetic factors, we shall present tabular and graphical descriptive summaries within subgroups, and use logistic regression to test for associations and provide estimates with 95% CIs;to evaluate if differences in myocardial recovery at 6 months are associated with demographics, genetics and CV comorbidities (diabetes, hypertension, heart failure and CAD/peripheral vascular disease), descriptive summaries, and linear and logistic regression methods will be applied;to understand the association between recovery status at 6 months and patient-reported QoL and functional capacity, descriptive methods, and linear regression will be used.

To assess whether there are characteristic ECG findings specific for SARS-CoV-2 myocarditis, measures of diagnostic performance will be calculated, and ROC analyses will be used.

In the coronary vascular sub-study, descriptive methods will be used to establish the nature and prevalence of myocardial ischaemia and microvascular dysfunction, and linear regression methods, including mixed effects methods for modelling myocardial blood flow within segments 1–16 of the American Heart Association 17-segment model, will be used to assess risk factors.

Throughout these analyses, levels of missing data will be reported, and regression models will be fitted using multiple imputation of missing predictor variables. Where appropriate, data from other cohorts will be used as control populations.

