### Data monitoring and linkage

The University of Glasgow will be coordinating centre for data and analysis and will hold identifiable data in secured databases to permit record linkage. The Universities of Leicester and Glasgow and NHS Laboratory Medicine (including the Biorepository) will undertake storage and/or analysis of blood samples (DNA, RNA, and small molecules).

As part of the patient consent process, it will be explicitly requested that anonymised data and images can be shared with other national and global research initiatives, for efficiency in data collection and sharing across other nationally prioritised UK COVID studies (e.g. C-MORE, P-HOSP-COVID and CISCO-19 [Cardiovascular and Pulmonary Imaging in SARS Coronavirus disease-19]) [47], as well as with other international CMR studies and registries e.g. the international SCMR COVID-19 registry. The principles set out in the 2016 Statement on data sharing in public health emergencies will be followed and it will be ensured that the World Health Organization (WHO) has rapid access to the emerging findings that could aid the global response.

As this is an observational study only serious adverse events (SAEs) that relate directly to the participation in the study procedures and sample collection will be reported to the sponsor and Ethics committee. All hospitalisations and deaths will be recorded as study outcomes.

The management of incidental findings of the research CMR scans will be performed at the individual site level according to the normal local practice and procedures.

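### Logistic regression is assigned to long-term clinical outcomes with no fixed analysis horizon, so the odds ratios depend on follow-up length and are biased if follow-up differs by risk factor

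*Protocol article*

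**What the plan says.** Under Statistical analysis, the second objective is "to assess how cardiac involvement and clinical outcomes associate with recognised risk factors for mortality in COVID-19", together with genetic factors. Besides descriptive summaries, the method is to "use logistic regression to test for associations and provide estimates with 95% CIs". One clause therefore covers a CMR finding at baseline and clinical events that accrue over time. Methods are named objective by objective (linear, logistic, ROC, mixed effects), and none is a time-to-event method.

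The follow-up behind those events is described three times:

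- Recruitment process and data collection: "Clinical follow up for vital status and cardiovascular events at 12 months (and up to 5-years) will be performed by recruitment sites", with record linkage in addition.
- Follow-up: "routine clinical outcome data will be collated up to 5 years post-infection".
- Fig. 2 legend: "Further follow up at 12 months will be conducted via examination of routine clinical data".

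Study outcomes lists long-term clinical outcomes among the main outcomes. Data monitoring and linkage adds: "All hospitalisations and deaths will be recorded as study outcomes". Appendix 1 defines the events, among them cardiovascular and non-cardiovascular death, myocardial infarction, stroke, pulmonary embolism and hospitalisation for heart failure or arrhythmia.

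Two further statements bear on incomplete follow-up. Consent procedures keeps the data gathered before a withdrawal in the final analysis. Statistical analysis provides multiple imputation for missing predictors only.

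**The concern.** A logistic model needs a yes/no outcome, and that outcome is well defined only if everyone is observed over the same window. The article gives 12 months and up to 5 years and does not say which window the regression uses. A patient who withdraws event-free at an early date must then be counted as a non-event or left out, and the article does not say which.

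An odds ratio for ever having had an event mixes the event rate with the time observed. The risk factors under test are age, sex, ethnicity, comorbidities and genetics. Age and comorbidity could plausibly relate to withdrawal and to non-cardiovascular death; ethnicity could relate to site and recruitment period across 25 hospitals. If so, a difference in time observed can appear as an association, or hide a real one, in one of the four primary objectives.

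**Working it through.** **Inputs from the document.** The method, follow-up statements, withdrawal rule and imputation rule are as above. The only quantitative planning figure is the work package-2 sample size.

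**Inputs that are assumptions.** The article gives no event rate, effect size, recruitment period or follow-up distribution. The main simulation assumes 333 patients, a binary risk factor present in half, exponential event times, a 12-month risk of 5%, 10% or 20% in the unexposed, a hazard ratio (HR) of 1 or 2, a two-sided 5% test and 400 replicates per scenario.

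**Step 1: the plan's own figure.** n = 1.96² × 0.12 × 0.88 / 0.035² = 331.1, rounded up to 332 (stated: 333). 333 / (1 − 0.10) = 370 (stated: 370). This reproduces within rounding, but concerns the precision of a prevalence and not clinical events.

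**Step 2: the odds ratio (OR) moves with the window.** Let S be the unexposed event-free probability at the horizon. With HR 2 the exposed probability is S², so OR = [(1 − S²)/S²] / [(1 − S)/S] = 1 + 1/S.

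- 12-month risk 10%: at 12 months S = 0.9, OR 2.11; at 5 years S = 0.9⁵ = 0.590, OR 2.69.
- 12-month risk 20%: at 12 months S = 0.8, OR 2.25; at 5 years S = 0.8⁵ = 0.328, OR 4.05.

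The hazard ratio is 2 throughout. At one stated horizon each OR is a defined quantity. Over an unstated mix of horizons it is not.

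**Step 3: follow-up that differs by risk factor, no true effect.** Take a 12-month risk of 10%, with the exposed followed for 1-4 years and the unexposed for 2-5 years, both uniform. Mean event-free probability = (0.9^a − 0.9^b) / [(b − a) × (−ln 0.9)].

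- Exposed: (0.9 − 0.6561) / 0.316 = 0.772.
- Unexposed: (0.81 − 0.5905) / 0.316 = 0.694.
- OR = (0.228/0.772) / (0.306/0.694) = 0.67, where the truth is 1.

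**Step 4: simulation, range over the three assumed risks.** FP is the false-positive rate at HR 1.

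| Follow-up | OR at HR 1 | FP, logistic | FP, Cox | OR at HR 2 | Cox HR at HR 2 |
|---|---|---|---|---|---|
| 12 months for all | 0.97-1.00 | 2-5% | 2-5% | 2.06-2.29 | 1.95-2.12 |
| 5 years for all | 0.98-1.02 | 2-5% | 3-5% | 2.28-4.02 | 1.97-2.00 |
| 1-5 years, unrelated | 0.97-1.02 | 5% | 4-5% | 2.13-2.55 | 1.97-2.04 |
| 1-4 vs 2-5 years | 0.62-0.69 | 18-59% | 5-7% | 1.42-1.59 | 1.96-2.04 |
| 1-3 vs 3-5 years | 0.39-0.47 | 59-99% | 4-7% | 0.98-1.02 | 2.02-2.03 |

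Power at HR 2 is practically equal in the first three rows (for 12 months: 38%, 60%, 93% logistic; 38%, 60%, 93% Cox). In the fourth row it is 28%, 46% and 56% for logistic against 74%, 96% and 99.5% for Cox.

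**Step 5: a common end date with unequal loss.** Assume a 5-year horizon for all, 40% exposed, a hazard of 8% per year, and loss of 3% per year in the unexposed and 10% per year in the exposed. With no true effect, logistic regression gave OR 0.81 with 14.5% false positives, and Cox gave HR 1.00 with 4.5%. At HR 1.8 the power was 54% against 89.5%. This is the lower end of the 15-60% range.

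**The case against.** The strongest reply is that logistic regression is not wrong in itself, and that the condition that makes it fail is not in the document. Analyses are to start only after follow-up data collection is complete, and 12 months is named as a definite time point in two places. Capture through national records may keep losses low. An event-by-12-months analysis fits all of this, and the first rows of the table show it would perform as well as Cox. Where follow-up varies but is unrelated to the risk factor, the false-positive rate stays near 5%, and the gap between the OR and HR 2 is partly the usual difference between the two measures. The article also introduces its methods as a broad outline and promises a signed analysis plan, which may fix the horizon.

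Most of that stands, and it limits the point. It does not remove it. Logistic regression is a method the article states, and no horizon goes with it. Completed data collection does not undo censoring by withdrawal or death. An analysis plan that follows the text as written takes over the problem.

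Three stronger readings are tempting, and the document supports none of them.

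- A reader might infer that patients will be analysed with 1 to 5 years of staggered follow-up. No such pattern, and no shortfall in any risk group, is stated.
- A reader might infer that time at risk is counted from infection, so that survival up to enrolment is credited. The Follow-up section says how long records are collated; it does not define an analysis origin. An error of origin would affect a Cox model equally.
- A reader might infer that ignoring competing death invalidates any yes/no analysis. At a fixed horizon with complete linkage, counting death from another cause as no event gives the odds of cumulative incidence, a legitimate target.

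**Conclusion.** The point holds in conditional form. Logistic regression is assigned to clinical outcomes that may run to 5 years, without a horizon or a rule for partial follow-up. With one complete common window it is sound. With unequal follow-up, the odds ratio depends on the mix of observation times. With follow-up that differs by risk factor, the association is biased.

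The error rates are illustrative and are not predictions for this cohort. They rest on assumed hazards, exposure prevalence and follow-up differences: about 5% false positives when follow-up is unrelated to the risk factor, about 15-60% when moderately related, and 59-99% in the strongly related scenario. The Cox results assume proportional hazards and censoring unrelated to event risk given the risk factor. Nothing here touches logistic regression for baseline CMR involvement, or the sample size.

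**What to change.** Split the clause for the second objective by outcome type.

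- **Baseline CMR involvement:** keep logistic regression.
- **Clinical outcomes:** use a time-to-event model, for example Cox regression, with cause-specific or Fine-Gray models where death competes with the event. Start time at risk at study entry and censor at last linkage or withdrawal.
- **Alternative:** keep logistic regression for clinical outcomes but restrict it to a stated fixed horizon, such as 12 months, with complete linkage, and say how patients who withdraw earlier are counted.

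The cost is wording in the analysis plan and the use of event dates from linked records. That those dates will be available is plausible but not stated, so it should be confirmed. The sample size of 370 and the visit schedule do not change.

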### Data monitoring and linkage

The University of Glasgow will be coordinating centre for data and analysis and will hold identifiable data in secured databases to permit record linkage. The Universities of Leicester and Glasgow and NHS Laboratory Medicine (including the Biorepository) will undertake storage and/or analysis of blood samples (DNA, RNA, and small molecules).

As part of the patient consent process, it will be explicitly requested that anonymised data and images can be shared with other national and global research initiatives, for efficiency in data collection and sharing across other nationally prioritised UK COVID studies (e.g. C-MORE, P-HOSP-COVID and CISCO-19 [Cardiovascular and Pulmonary Imaging in SARS Coronavirus disease-19]) [47], as well as with other international CMR studies and registries e.g. the international SCMR COVID-19 registry. The principles set out in the 2016 Statement on data sharing in public health emergencies will be followed and it will be ensured that the World Health Organization (WHO) has rapid access to the emerging findings that could aid the global response.

As this is an observational study only serious adverse events (SAEs) that relate directly to the participation in the study procedures and sample collection will be reported to the sponsor and Ethics committee. All hospitalisations and deaths will be recorded as study outcomes.

The management of incidental findings of the research CMR scans will be performed at the individual site level according to the normal local practice and procedures.

## Discussion

The COVID-HEART study is a longitudinal, multicentre, observational cohort study of UK patients presenting with COVID-19 infection and positive troponin, who are either recovering in hospital or were recently discharged. It aims to utilise CMR in evaluation of the nature and extent of myocardial injury and subsequently, myocardial recovery in these patients, and to examine the impact of myocardial recovery status on quality of life and functional capacity. Additional investigations include laboratory testing, which will encompass routine tests, novel cardiac biomarkers, and genetic analysis. These results will be shared with other global initiatives to address genetic susceptibility to COVID-19. Furthermore, ECGs will be investigated with the aim of identifying sensitive and specific changes that would allow diagnosis of myocarditis without the need for invasive testing.

As COVID-19 is an unprecedented global health emergency and previous studies showed that a significant proportion of patients had myocardial injury, it is important to further understand the underlying pathophysiology, risk factors and long-term outcomes. Therefore, the results of the COVID-HEART study, and the results of other registries examining myocardial injury (e.g. PHOSP-COVID, ISRCTN10980107; MOIST, NCT04525404; MYOCOVID, NCT04375748; MIIC-MI, NCT04412369; CARDOVID, NCT04455347; CISCO-19, NCT04403607), may have significant clinical implications on the assessment and management of these patients. Furthermore, the new knowledge from these studies will help inform disease-targeted therapy development, for the prevention and treatment of cardiovascular complications in COVID-19.

## Data Availability

The datasets used and/or analysed during the current study will be available from the corresponding author on reasonable request. Anonymised data may be shared with other COVID-19 global initiatives.

## Appendix 1: Summary definitions of clinical outcomes

A pre-specified, signed, *Clinical Outcomes Charter* will be provided to each recruitment centre. This will contain detailed endpoint definitions to facilitate consistent local adjudication and unbiased reporting. Endpoint definitions will align with the 2014 American College of Cardiology/American Heart Association Key Data Elements and Definitions for Cardiovascular Endpoint Events in Clinical Trials [48]. In brief, these endpoints will include:

1. *Cardiovascular death* is a defined as death occurring secondary to an acute myocardial infarction, sudden cardiac death, heart failure, stroke, death resulting from cardiovascular procedures or death due to cardiovascular haemorrhage.
2. *Non-cardiovascular death* is defined as any death with a specific cause that is not thought to be due to a cardiovascular cause. There should be unequivocal and documented evidence of a non-cardiovascular cause of death.
3. *Myocardial infarction* is defined as elevation of cardiac biomarkers above the 99th percentile of the upper reference limit in the setting of an appropriate clinical presentation in combination with diagnostic ischaemic electrocardiographic changes. Specific clinical classification of different types of myocardial infarction will be assigned from the 4th Universal Definition of Myocardial Infarction [12].
4. *Coronary artery revascularisation*, either by percutaneous coronary intervention (PCI) or coronary artery bypass graft surgery (CABG).
5. *Transient ischaemic attack* is defined as an episode of focal neurological dysfunction resulting from brain, retinal and spinal cord ischaemia, that is transient in nature and resolves within 24 h.
6. *Stroke* is defined as a focal or global neurological dysfunction secondary to brain, retinal or spinal cord injury resulting from haemorrhage or infarction.
7. *Pulmonary embolism* is defined based upon clinical evaluation and a diagnostic imaging test, ideally, computed tomography (CT) pulmonary angiography. If ventilation/perfusion scintigraphy is used, then the diagnosis may be accepted based on clinical evaluation and a high probability scan. The clinical evaluation and diagnosis of pulmonary embolism should align with the 2019 ESC Guidelines for the diagnosis and management of acute pulmonary embolism [49].
8. *Deep venous thrombosis (DVT)* diagnosis should be established based on a clinical evaluation, D-dimer elevation and imaging findings (duplex ultrasound or CT angiography).
9. *Myopericarditis* diagnosis will be adjudicated based upon the 2013 Position Statement of the European Society of Cardiology Working Group on Myocardial and Pericardial Diseases.(50)
10. *Hospitalisation for other cardiovascular cause*:
  - *Heart failure* events are defined as hospitalisation for heart failure or an urgent outpatient visit. A heart failure hospitalisation event must fulfil the following criteria: primary admission diagnosis is heart failure, the patient experiences either worsening of heart failure symptoms or a new symptom, and requires an increase in therapy.
  - *Arrhythmia* defined as hospitalisation with an arrhythmia (atrial, supraventricular and/or ventricular or brady-arrhythmia) documented by electrocardiography (single- or multi-lead) with a change in treatment (withhold, change in dose of existing medication, prescription of new medication for arrhythmia) and/or pacemaker therapy.
  - *Chest pain/unstable angina* defined as an emergency/unplanned admission to a hospital setting that results in at least one overnight stay (i.e. a date change) with cardiac ischaemic-type symptoms at rest or minimal exertion.

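### As written in Appendix 1, outcome myocardial infarction requires diagnostic ECG changes with no imaging or angiographic route; less firmly, outcome DVT lists D-dimer elevation alongside imaging

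*Protocol article*

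**What the plan says.** Appendix 1, item 3 says that myocardial infarction "is defined as elevation of cardiac biomarkers above the 99th percentile of the upper reference limit", and adds that this must occur "in the setting of an appropriate clinical presentation in combination with diagnostic ischaemic electrocardiographic changes". The sentence after it reads "Specific clinical classification of different types of myocardial infarction will be assigned from the 4th Universal Definition of Myocardial Infarction". That covers the type of infarction, not an alternative way to qualify as one.

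Appendix 1, item 8 says that a DVT "diagnosis should be established based on a clinical evaluation, D-dimer elevation and imaging findings (duplex ultrasound or CT angiography" in parentheses. Item 7, on pulmonary embolism, says that the event "is defined based upon clinical evaluation and a diagnostic imaging test, ideally, computed tomography (CT) pulmonary angiography", and refers to a guideline for the details. It names no D-dimer element.

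Two statements frame these items. Of the Clinical Outcomes Charter, the appendix says: "This will contain detailed endpoint definitions to facilitate consistent local adjudication and unbiased reporting". It also says: "Endpoint definitions will align with the 2014 American College of Cardiology/American Heart Association Key Data Elements and Definitions". The Analysis plan section names Appendix 1 as the definition set by which individual hospitals adjudicate events, and places that set within the signed charter.

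**The concern.** Item 3 joins its three elements so that all must be present. Evidence from angiography, echocardiography or CMR has no part in it. That sits oddly with the rest of the protocol. The section on recruitment and data collection lists these modalities as source data, and the Fig. 1 caption presents an ischaemic-pattern scar on late gadolinium enhancement as an example of infarction.

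Item 8 treats DVT differently from its sister event. Read literally, a duplex-positive DVT with no D-dimer result falls short, while an embolism shown on CT with no D-dimer result meets item 7. No reason is given.

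Long-term clinical outcomes are a main outcome, followed for up to 5 years. The second primary objective relates them to age, sex, ethnicity, comorbidities and genetic factors by logistic regression. The ECG data section also looks for prognostic ECG findings in the same patients. If an outcome can be recorded only when the ECG shows certain changes, its detection may depend on the patient's ECG, which is itself a candidate predictor. This point concerns new events in follow-up, not the index injury.

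**Working it through.** **No plan figure to reproduce.** The protocol gives no event rates, no share of infarctions without diagnostic ECG changes and no share of DVTs without a raised D-dimer. Its only derived figure, the sample size of 333 (370 with 10% drop-out), rests on a 12% prevalence of myocardial involvement and does not depend on these definitions. The check is therefore to apply the written definitions to concrete cases.

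| Follow-up event | Result under the written item | Where else it may be recorded |
|---|---|---|
| New troponin rise, fitting presentation, diagnostic ECG | Meets item 3 | – |
| Same, ECG non-diagnostic, culprit lesion at angiography | Does not meet item 3 | Item 4 if revascularised; item 10 if an unplanned overnight admission; item 1 if fatal |
| Same, ECG non-diagnostic, new ischaemic scar on CMR | Does not meet item 3 | LGE outcome, if seen on a study scan; items 1, 4 or 10 as above |
| DVT on duplex, D-dimer not raised or not measured | Does not meet the item 8 list read literally; the verb is advisory | No other named thrombosis item |
| Embolism on CT, D-dimer not measured | Meets item 7 as worded | – |

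No other section supplies an alternative entry route for infarction or DVT.

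**Scale, by assumption only.** If a share s of true infarctions lacks diagnostic ECG changes, the number that qualify out of 20 is 20 × (1 − s):

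- s = 5%: 20 × 0.95 = 19
- s = 20%: 20 × 0.80 = 16
- s = 40%: 20 × 0.60 = 12
- s = 50%: 20 × 0.50 = 10

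Both the 20 and the shares are assumed. The range is too wide to serve as an estimate. The same formula applies to DVT, with s as the share lacking a raised D-dimer.

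**Effect on an association, by assumption only.** Take true risks of 10% and 5% in two risk groups, so a ratio of 2.0:

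- Equal detection (80% and 80%): 8% against 4%, ratio 2.0, unchanged.
- Lower detection in the high-risk group (60% and 80%): 6% against 4%, ratio 1.5.
- Higher detection in the high-risk group (80% and 60%): 8% against 3%, ratio 2.7.

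The direction depends on which group more often lacks the required item. The protocol does not say.

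**The case against.** The strongest reply is that Appendix 1 is a summary, given in brief, of a charter that is not shown, and that the definitions are to align with a named external standard. The charter may already admit imaging evidence. This stands as a limit: a reader might infer that proven events will in fact go uncounted, and the documents do not support that. It does not remove the point, because the Analysis plan section names Appendix 1 as the set that sites use. If the charter is wider, the published definition misstates the endpoint; if it is not, the restriction is real.

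Second, item 8 is advisory, whereas the same appendix uses mandatory language for heart failure hospitalisation. This also stands. A reader might take D-dimer as a firm gate for DVT; the text does not go that far. What remains is an unexplained difference from item 7.

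Third, the events are not lost to the study. LGE is its own main outcome, all hospitalisations and deaths are recorded, and several other items could capture the event. This largely stands: what changes is mainly the label. The LGE route is limited, however, because the scheduled study scans end at 6 months while clinical follow-up runs to 5 years.

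Fourth, requiring ECG evidence can be defended on specificity, since the Background lists many causes of troponin release other than infarction. That is fair for troponin with symptoms alone. It is weaker where angiography or imaging also shows a new infarction.

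Finally, a reader might conclude that associations are biased towards the null, or that DVT and embolism rates cannot be compared. The first needs facts on who has non-diagnostic ECGs, which the protocol does not give. For the second, the protocol plans no such comparison.

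**Conclusion.** The point holds as a statement about the written definitions. Item 3 makes diagnostic ECG changes a required element of outcome infarction and leaves out evidence that the study itself collects and elsewhere reads as infarction. The infarction half is firm on the text; the DVT half is an inconsistency in advisory wording.

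The size of any undercount and the direction of any bias cannot be determined from the documents. The calculations show only what follows under stated assumptions. Whether events are undercounted in practice depends on the charter and on the external standard, neither of which is available here. The correction is worth making because it affects a main outcome adjudicated locally across 25 hospitals, and because it is cheap.

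**What to change.** Make the following changes in Appendix 1, and in the Clinical Outcomes Charter if it carries the same wording.

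1. Item 3: require a new troponin rise and an appropriate clinical presentation, together with either diagnostic ischaemic ECG changes or imaging or angiographic evidence of new infarction. Stating that the rise is new matters because every participant enters with a raised troponin.
2. Item 8: define DVT by clinical evaluation plus diagnostic imaging, with D-dimer as supportive information only, in line with item 7.
3. Confirm that both items agree with the charter and with the 2014 ACC/AHA endpoint definitions that the appendix names. If the charter is already wider, only the appendix needs correcting.

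The cost is two wording changes, slightly more record review at sites using sources already listed, and slightly lower specificity for infarction. The sample size is unaffected.
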